**4. Introduction**

**Background of the study**

Mental health is an essential element for the well-being of all individuals, families, and societies. It is fundamental to the population's health, quality of life and social and economic stability (Moksnes & Reidunsdatter, 2019). World Health Organization (WHO) has defined mental health as "a state of well-being in which the individual realizes his or her own abilities, can cope with the normal stresses of life, can work productively and fruitfully, and is able to contribute to his or her community” (Srivastava, 2011; Galderisi et al., 2017).

Children and adolescents' mental health are a global public health issue widely recognised as a critical component of research and government intervention (Barker et al., 2019). Worldwide, it is estimated that between 10% and 20% of children and adolescents suffer from mental health problems (Barker et al., 2019; Teresa Gutmann et al., 2019).

Mental health conditions account for sixteen per cent of the global burden of disease and injury in people aged between ten to nineteen years (WHO, 2018). Half of adult mental health conditions arise in the middle of Adolescence, while three-quarters of them occurring by the middle of their twenties (WHO, 2019).

Depression and anxiety are the most frequently encountered mental health problems, which significantly impact children and adolescents. These disorders have been shown to increase the risk of adverse outcomes such as impairment, loss of productivity and community involvement, decreased educational performance, increased likelihood of engaging in risky behaviours, disability, and increased self-harm and suicide rates (Dray et al., 2015). Worldwide, depression is the fourth leading cause of illness and disability among adolescents aged 15-19 years and fifteenth for those aged 10-14 years. Meanwhile, anxiety is the ninth leading cause among 15-19 years old adolescents and sixth for those aged 10-14 years old (WOH, 2018).

Migration is also stressful for children and youth and their families during immigration and even after the settlement (Triantafyllou et al., 2018). Children of immigrants face social and emotional changes during the development stage, and they face challenges as their families adopt new cultures and languages within an unfamiliar setting. The emotional well-being of children from immigrant families is a critical public health concern. The most common mental health disorders affecting these children are manifested externally as disruptive behaviours, arguing, fighting, rule-breaking, or internally with features such as pessimistic thinking, sadness, anxiety, and loss of interest in daily activities (Kim et al., 2018).

Many studies confirm migration as a high-risk factor for mental health problems. Migration-related stress, economic disadvantages, and discrimination increase the vulnerability of the persons concerned. Migrant children and adolescents are more endangered than their native peers (Teresa Gutmann et al., 2019). Therefore, it is essential to develop and design education programmes that educate and support a diverse range of teenagers who may be at risk for developing mental health difficulties, especially those susceptible to having issues with their internalising problems (Cho, 2016).

Students spend a substantial amount of their day in school. The school setting and atmosphere are ideal for targeting all individuals, particularly those with severe symptoms who may not have sought counselling or are at risk of becoming symptomatic due to external stressors or internal vulnerabilities and those who may develop symptoms in the future (Calear et al., 2018).

School plays a vital role in developing cognitive and social skills and coping mechanisms to deal with stress. Additionally, school-based mental health programmes appear to decrease the stigma surrounding mental health and increase the frequency of consumption, especially among ethnic minorities (van Loon et al., 2020). School-based programmes eliminate many barriers, including cost, location, time, transportation, and stigmatisation (Calear et al., 2018).

Life Skills Program is one of the organized educational interventions that aim to improve mental health and boost positive and adaptive behaviour among the target individuals (UNICEF, 2015). Life skills intervention has effectively targeted different areas of adolescent health, including psychosocial, physical, and sexual and reproductive health outcomes (Singla et al., 2020). Life skills programs also play an essential part in enhancing students' academic success and non-academic areas, such as strengthening coping mechanisms and developing self-confidence and empathy (State, 2012).

Life Skills Education includes activities that support critical and creative thinking, coping with emotions and stress, self-awareness and empathy, decision-making and problem-solving, communication skills, and interpersonal relations (Nasheeda et al., 2019). Previously, online-based interventions have effectively addressed common mental health conditions among adolescents by reducing the current burden on traditional counselling services (El Morr et al., 2020) and significantly improving mental health (Spijkerman et al., 2016; Wong et al., 2014).

In this regard, this research aims to examine and determine the effect of online life skills-based intervention in reducing depression, anxiety, and stress among Arabic adolescents at Arabic schools in the Klang Valley, Malaysia, increasing their self-efficacy and coping skills.

**Problem statement and study rationale**

Migrant children and adolescents are at increased risk of anxiety and depression. The reasons for that due to asymmetric acculturation within the family, lack of adequate support from their parents and restrictive processes due to discrimination, poor socioeconomic status, living in more crowded houses and settlements in districts with insufficient infrastructure in cities and inadequate access to the healthcare system (Akkaya-Kalayci et al 2017; Atramentova et al 2018; Kim et al., 2018; Gatt, J. M.,2020; Lachal, J., et al 2020).

So, compared to the rest of the world, most Arabic populations are below 25 years (Abou Abbas & AlBuhairan, 2017). Arab adolescents bear a higher mental and behavioural disorders burden. They face additional critical challenges that can negatively affect their mental health. These include high illiteracy rates, sharp disparities in education and deterioration of education quality, inadequate health services, and poor access to health facilities, especially mental health facilities. These risk factors are further exacerbated by the dramatic changes that many Arab countries are experiencing due to severe armed conflicts, violence, and suppression (Latefa A. Dardas et al., 2016).

Among Arabic children and adolescents in The Eastern Mediterranean Region (EMR), mental disorders are estimated between10% to 36%. These figures are similar or slightly higher than the global estimate of 20% (Desouky et al., 2015). Between 1990 and 2015, there is a clear pattern toward an increasing burden of mental disorders in Arabic countries when compared to the international estimate. Conditions such as depression and anxiety account for most of the burden (Rahman, 2018), and represent a more significant percentage of disability-adjusted life years (DALYs) lost among Arab teenagers, with a high rate in armed conflict and displacement areas like Iraq, Lebanon, Algeria, and Palestine (Obermeyer, Bott, and Sassine 2015). Figure 2 illustrate that mental and behavioural disorders represented the most common cause for disability-adjusted life years (DALYs) among adolescents aged (10-19).

Palestine, for instance, had the most considerable disadvantage of mental disorders; this burden is likely to increase due to the unrest and conflict; 54.4% of Palestinian boys and 46.5% of Palestinian girls (age 6–12 years) were estimated to have mental disorders. Moreover, 37.4% of Iraqi schoolchildren were estimated to suffer from mental illnesses, and 33.5% of Syrian refugees in Turkey had Post-Traumatic Stress Disorder (Charara et al., 2017).

**Significance of the Study:**

Promoting and improving mental and emotional health is critical especially when considering migrant children and adolescents as they are part of the society and they will eventually become adults, they can engage with healthy lifestyles and reduce the burden of diseases and empower the abilities to succeed in adulthood.

This study can help Arabic students to reduce screening barriers apart from bridging the gap due to limited access to information and service for Arabic adolescents. This study also may contribute to the credibility of the effectiveness of utilizing a life skills education intervention in educating Arabic secondary school students about mental health and how to cope with daily stressors.

This research will directly benefit the students, their families, and friends, as well as to provide information to the researchers and health care workers who strive to produce beneficial interventions for adolescent migrants. Our finding also will benefit many organisations and high authorities such as Arabic embassies and Arabic school administrators, and the ministry of health and education of Arabic countries to improve mental health among Arabic children and adolescents. We expect that the interventions will promote mental health and empower teenagers with the essential life skills resources to reach the desired ability and overcome challenges.

Consequently, implementation of such programs for adolescent mental health can facilitate the development of adolescent mental health services delivered through the existing health and social services. Promote coordinated inter-sectoral action for positive mental health and prevention of mental disorders, so this will establish linkages between education and health services to enable early recognition and management of any mental, neurological and substance use disorders. Facilitate the strengthening of health systems and promote monitoring, evaluation and research.

**5. Research Question(s)**

What is the effect of online Life Skills-based intervention on depression, anxiety and stress levels, self-efficacy and coping skills between and within the intervention and control groups immediately post-intervention, and 3 months after the intervention and even after adjusted for covariate variables?

**6. Research objectives**

To determine the effect of online Life Skills based intervention on (depression, anxiety and stress), self-efficacy and coping skills among Arabic adolescents (14–18 years of age) in Klang Valley, Malaysia.

**7. Research methodology**

- **Research design**

This study is quantitative in nature and experimental in design. Specifically, this is a parallel cluster‐randomized controlled trial (cRCT). The schools will be the unit of randomization (clusters). The trial will be used to assess the effectiveness of online life skills program in reducing mental health problems (depression, anxiety and stress) among Arabic adolescents in Klang Valley, Malaysia. There are around 18 well‐known Arabic schools in Klang Valley area, with students from different Arab countries (i.e., Yemen, Iraq, Egypt, Libya, Syrian, Saudi Arabia, and etc).

- **Study location (state and justify the exact study location)**

The study will be located in Klang Valley, in the state of Selangor, Malaysia.

**Study duration:**

It is expected to be 3-4 years to complete the study from 2020-2024.

**- Study population (target population, sampling frame, sampling unit).**

**Target population**

The target population is all Arabic adolescents aged (14 -18years) at Arabic schools, in Klang Valley, Malaysia.

**Sampling Frame**

The sampling frame is a list of all eligible Arabic schools which located in Klang Valley.

**Sampling Unit**

The sampling unit of this study is the Arabic students both males and females (14-18years old) in the Arabic schools, and who will be fulfilled the inclusion and exclusion criteria during the time of the study.

- **Subject criteria** **(inclusion and exclusion criteria)**

**The inclusion criteria for schools are:**

(1) Arabic schools that agree to participate.

(2) The Arabic schools that located in Klang Valley.

**The inclusion criteria for students:**

(1) Arabic Students aged from 14 to 18 years old.

(2) students who give the assent from them and consent from their parents.

(3) student who have scored mild to extremely severe score in depression, anxiety and stress based on baseline assessment.

**The exclusion criteria for schools are:**

(1) non-Arabic schools that have Arabic students.

(2) Schools who refuse to participate in the study.

**The exclusion criteria for students:**

(1) students who refuse to participate.

(2) Students who have hearing limitations, because they cannot interact during the online session.

(3) Students who have diagnosed or treated of mental health problems before based on their school file, because it may interfere with the effect of the program.

***-* Sample size estimation (to consider non-response or attrition rate)**

**Sampling size**:

The total sample size needed will be calculated by applying the formula for two population means

Means and standard deviation used for the intervention group and control group are based on the estimation offered in a previous RCT (Osborn et al., 2020). Calculation of the required sample size in this study was performed based on the guidelines in the CONSORT for cluster RCTs. By considering the account intra-class correlation coefficient (ICC), it is necessary to multiply the sample size in RCTs by design effect=1+(m–1)*ICC, where m is the average cluster size. The formula for fixed number of clusters with unequal cluster sizes will be used. Adequate sample size after Adjust for attrition rate and expected proportion eligible and multiply with design effect= 165. Therefore, the total sample size required was 165 students. Number of clusters (schools) = estimated sample size/ cluster size = 165/54=3. Following the sample size calculation, the number of schools needed will be 3 schools. However, in order to get the required sample size, a total number of 12 schools that met the inclusion and exclusion criteria during the study time will be included in the study.

***-* Sampling method and subject recruitment**

**Sampling Method**

A cluster sampling will be used for selection of the schools. There are 12 Arabic schools in Klang Valley that meet the inclusion and exclusion criteria for this study and they will be selected to be included in the study. In order to get the required sample size, the total number of 12 schools that met the inclusion and exclusion criteria during the study time will be included in the study. Each of the schools (clusters) will then receive a serially numbered unique code. The clusters will be assigned to the intervention or control group by the ratio 1 to 1 and will be performed using block randomization using random block sizes of 2 and 4 by an independent statistician from Universiti Putra Malaysia. Therefore, 6 clusters will be in the intervention group and 6 clusters will be in the control group. Then all the students (aged 14-18 years) in the selected school, and who give assent and consent from their parents to participate will be included in the study.

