**Recruitment**

For the purpose of eligibility assessment, the researcher will approach all Arabic schools in Klang Valley in Malaysia and invite these schools through formal invitation letters issued by the researcher’s university.

After getting the permission from responsible authorities of all Arabic schools (Appendix C), short online meeting will be arranged for each school. During the meeting, the researcher will explain the objectives and benefits of the study as well as the inclusion and exclusion criteria to the participants. Then a written consent will be sent to students and their parents. The students who agree to participate will be asked to answer the baseline data questionnaires (screening for eligibility). After the life skill educational intervention will be delivered to the intervention group, post-intervention assessment questionnaire will be distributed two times, immediately after the intervention completed and 3-month post-intervention for those who are eligible in screening stage.

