**Randomization and Concealment Allocation**

The schools will be allocated randomly to intervention and control groups by using block randomisation after cluster size will be identified. To ensure allocation concealment, the allocation sequence of the selected schools will be assigned to a control group and an intervention group by the ratio 1 to 1 using random block sizes of 2 and 4 by an independent statistician from Universiti Putra Malaysia. To ensure allocation concealment, each cluster will receive a randomly generated treatment allocation unique code within serially numbered sealed opaque envelope. Then the research assistant will distribute the sealed opaque envelopes to the schools and the envelopes will be opened later and assigned the clusters according to their unique codes to the intervention or the control group based on the list codes generated by the software. Then the students will be assigned to the intervention group and to the control group.

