***-* Data collection (state the method, ensure privacy and confidentiality, quality assurance)**

At baseline before conducting the Life skill education program, questionnaires include (socio-demographic, Depression, anxiety and stress scale DASS-21, self-efficacy, and Brief Cope Scale) will be distributed to both intervention and control groups. The follow-up evaluation will be carried out immediately, and three months after the educational intervention for all students in the intervention group and the control group. The only exception being the questions on socio-demographics will be excluded for post-tests evaluation.

Data will be held in a confidential and anonymous manner ***and no third party “will have access or visibility to your data. This will be used for research purposes only***

9- **Study flowchart (diagrammatic illustration)**

Diagrammatic illustration of the study framework which provides a context to explain the study finding

[figure not shown]

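### The protocol does not settle whether students consent and are screened before or after their school's allocation is disclosed, which leaves room for recruitment bias

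*Protocol*

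**What the plan says.** Four sections of the protocol bear on the order of events.

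- **Sampling Method.** Schools are coded and block-randomised 1:1. "Therefore, 6 clusters will be in the intervention group and 6 clusters will be in the control group". The next sentence turns to students: "Then all the students (aged 14-18 years) in the selected school, and who give assent and consent from their parents to participate will be included".
- **Recruitment.** After permission from the school, the researcher holds an online meeting, explains the study's benefits and its entry criteria, and sends consent forms. "The students who agree to participate will be asked to answer the baseline data questionnaires (screening for eligibility"). The section does not say whether allocation has been made or disclosed by then.
- **Randomization and Concealment Allocation.** "The schools will be allocated randomly to intervention and control groups by using block randomisation after cluster size will be identified". A research assistant distributes sealed opaque envelopes to the schools, and "the envelopes will be opened later and assigned the clusters according to their unique codes". The section ends: "Then the students will be assigned to the intervention group and to the control group".
- **Data collection.** The baseline questionnaires, given before the programme starts, "will be distributed to both intervention and control groups".

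Three other sections set the context. The student inclusion criteria require a baseline score of mild or worse. Research tools/instruments makes the DASS-21 the screening instrument. Section 11 names the change in mean depression, anxiety and stress score as the primary outcome.

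**The concern.** In a cluster trial, concealing the school sequence protects the assignment of schools. It does not protect the later enrolment of students within those schools. If pupils, parents or the recruiting researcher know the arm when consent is sought, willingness to join can differ between arms. So can the answers given on a self-report questionnaire whose entry threshold has just been explained.

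This trial is exposed on both counts, because each student must consent and because entry depends on a self-reported score on the primary outcome scale. The arms could then differ for reasons other than chance, both in measured baseline severity and in unmeasured traits such as motivation. Covariate adjustment deals with the first only in part and with the second not at all. Once students have been enrolled knowing their arm, analysis cannot fully repair it.

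**Working it through.** **Order of steps.** The protocol gives no figure to reproduce, so the first check sets the sections side by side.

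| Section | Order it implies | Link between disclosure and completed consent or screening |
|---|---|---|
| Sampling Method | schools assigned, then consenting students included | none |
| Recruitment | consent, screening, later the programme | allocation not mentioned |
| Randomization and Concealment Allocation | cluster size known, schools allocated, envelopes opened later, students assigned | none |
| Data collection | baseline given to groups named by arm | none |

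Cluster size in the third row is undefined. It could be the school roll, in which case nobody need have consented, or the number of consented or eligible students, in which case screening is finished. The protocol does not say who opens the envelopes or when. None of the sections says that the recruiter, students or parents are unaware of allocation. A team could follow Sampling Method literally and still be compliant.

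**Illustration of size. The consent rates, cut-offs and severity distribution are assumptions, not protocol figures.**

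Severity is one standard normal scale across all students. In control schools everyone consents at 50%. In intervention schools the most distressed third consent at 80% and the rest at 50%. Only students above a screening cut-off c are enrolled.

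The top third starts at z = 0.431, where the normal density is φ = 0.3636. The contribution of a band to the mean is the density at its lower edge minus the density at its upper edge.

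- Top third: share 0.3333, contribution 0.3636.
- Eligible students below the top third: share 0.6667 − Φ(c), contribution φ(c) − 0.3636.

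*c = −0.5.* Lower band: share 0.6667 − 0.3085 = 0.3581, contribution 0.3521 − 0.3636 = −0.0115.
- Control mean = 0.3521 / 0.6915 = 0.509
- Intervention mean = (0.8 × 0.3636 − 0.5 × 0.0115) / (0.8 × 0.3333 + 0.5 × 0.3581) = 0.2851 / 0.4457 = 0.640
- Gap = 0.13

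*c = 0.* Lower band: share 0.1667, contribution 0.3989 − 0.3636 = 0.0353.
- Control mean = 0.3989 / 0.5 = 0.798
- Intervention mean = (0.2909 + 0.0177) / (0.2667 + 0.0833) = 0.3086 / 0.35 = 0.882
- Gap = 0.08, or 0.14 in SDs of the enrolled sample

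*c at or above 0.431.* Every eligible student within an arm consents at the same rate, so the gap is 0.

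That zero comes from the stepped consent pattern. If instead the log-odds of consent in intervention schools rise smoothly by 0.25 to 1.0 per SD of severity, the gap at c = +0.5 is 0.055 to 0.109 enrolled-sample SD. Across cut-offs from −0.5 to +0.5 it runs from 0.055 to 0.233.

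**What baseline adjustment cannot remove.** Suppose consent in intervention schools follows an unmeasured trait with the same slopes, and the trait correlates 0.1 to 0.3 with outcome. Bias is the correlation times the shift in the trait's mean among consenters, which is about 0.12 to 0.41 SD. This gives 0.1 × 0.12 = 0.012 up to 0.3 × 0.413 = 0.124 SD. With no differential consent it is zero.

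**The case against.** The best defence is that the section devoted to randomisation can be read as safe. Schools are allocated "by using block randomisation after cluster size will be identified", envelopes are opened afterwards, and students are then assigned. Recruitment describes consent and screening with no hint of a known arm. The sentence under Sampling Method may describe only the second sampling stage, and naming both groups under Data collection may be shorthand for all participants. Generating a sequence is also not the same as disclosing it. With an independent statistician and sealed envelopes, assignment could come first and still be unknown at consent.

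This stands to the extent that a reader might infer that schools are definitely unmasked before students consent. The text does not establish that, because no section states disclosure before consent. It does not remove the problem, because no section states the reverse either, and the literal order under Sampling Method is the unsafe one.

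A reader might also ignore screening, obtain a gap of (0.8 × 0.3636 − 0.5 × 0.3636) / (0.8 × 0.3333 + 0.5 × 0.6667) = 0.109 / 0.60 = 0.18 SD, and set it against a treatment effect. The documents do not support that use:

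- The trial enrols only students who screen positive.
- The figure is a baseline gap, while the outcome is a change in score and the GEE includes the pre-intervention time point and covariates.
- The protocol states no target effect to compare it with.
- Reversing the rates within intervention schools gives about 0.16 in the other direction, not a mirror image.

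**Conclusion.** The protocol is inconsistent on a step that decides whether enrolment is protected from knowledge of allocation. Sampling Method, with some support from Data collection, puts assignment before consent. The randomisation section is open, and nothing reconciles them. Recruitment bias is therefore possible, not demonstrated.

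Under the assumed 80% and 50% consent rates the baseline gap is 0 to about 0.13 SD on the all-student scale, for cut-offs from the top third down to −0.5 SD. Only part of that would carry into the effect estimate. The direction depends on who is drawn in, and the gap vanishes if consent does not differ by arm. The conclusion rests on the conflict in the text, not on these figures. It should be resolved before any student is consented, because the harm cannot be fully undone later and the correction is cheap.

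**What to change.** State one order, in the same terms, under Sampling Method, Recruitment, Randomization and Concealment Allocation, and Data collection:

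1. Parental consent, student assent, DASS-21 screening and all baseline questionnaires are completed and locked in all 12 schools.
2. Only then is any envelope opened.
3. No student enters the analysis set after that point.

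Define cluster size in the randomisation section so that it fits this order.

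If the order proves unworkable, the fallback is recruitment by someone unaware of allocation, with the numbers approached, consented, screened and eligible reported by arm and school. This is weaker, since students and parents may still know their arm.

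The cost is wording, plus a short wait for the schools that finish baseline first.
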